### Plans to promote participant retention

In order to promote retention, we have prepared a video about how to execute the project and details of the project process to reduce possible anxiety and answer the questions. Participants can watch it before testing day, and they are encouraged to share their questions or concerns. All participants are welcome by one of the trained researchers in the testing day and they were all accompanied until the end of the experiment. Any adverse effect during the study is recorded in detail, and they also have the contact number of researchers for advice in case of any possible side effect in the following days. They are informed that they have the option to withdraw from the study at any time. If this occurs, their data will be removed from the result of the study.

### Participants

We plan to enroll 64 subjects from specialized nutrition clinics by flyer advertising. We also made a video to get people more familiar with our project. Participants must follow all of the inclusion criteria below:
Age ≥ 18 and < 61 years oldRight-handednessPersian speakingBMI: 25–35 kg/m^2^Frequent food cravings (≥ 3 per day during last month, as assessed by self-report questionnaire)Being responsive in food cue-reactivity screening at baseline (defined as mean craving scores (> 70) in food-related images on the Visual Analog Scale (0–100))

The participant with any of the following criteria will be excluded from the study:
Unwillingness or inability to complete any of the major aspects of the study protocol including food cue rating or behavioral assessmentsComorbid psychiatric disorders (i.e., depressive, bipolar, or psychotic disorders), which are evaluated by a mental health specialistActive suicidal ideation with intent or plan as determined by self-report or assessment by a mental health specialist during the initial screening or any other phase of the studyUnstable medical disorder reported in subject’s medical history or by a clinician assessmentNon-correctable vision or hearing problemsPersonal or family history of seizuresHistory of strokeAny other condition the research team feel would put the subject at risk for entering the studyContraindication to tDCS (pacemaker, a metal embedded in the scalp or brain, skin lesions at the site of stimulation, and history of head injury or neurosurgery) and MRI (claustrophobia, metallic implants, ferromagnetic metals in the scalp or brain, and pregnant women)

Concomitant care and interventions prohibited during the trial will be the recent use of diabetes medication or insulin injection or a medical indication for use during the study period, the use of medications that can affect appetite or weight (e.g., orlistat, sibutramine, topiramate, bupropion), and participation in weight loss program or non-invasive brain stimulation therapy during the study.

If all eligibility criteria are reached and participants provide written informed consent for study participation, they will be included in the study sample. Eligibility will be determined by the trained study staff during screening and baseline assessments.

### Intervention

Transcranial direct current stimulation will be administered via a battery-driven stimulator (DC-Stimulator Plus, Neuroconn GmbH, Germany). Direct current will be transferred by two saline-soaked sponge electrodes (7 × 5 cm^2^). For effective bilateral tDCS, the tDCS montage will comprise placement of the anode over the right DLPFC and the cathode over the left DLPFC which corresponds to the F4 and F3 areas, according to the 10–20 EEG system. Active tDCS will be delivered with a constant current of 2 mA for 20 min (ramp-up/down: 30 s). The montage and dose of stimulation were chosen based on previous studies for food craving in healthy adults [30–32]. For the sham group, the same electrode position and ramp-up/down time will be used, but the 2-mA current will be delivered only during the first 1 min of the 20-min stimulation period to elicit a transient tingling sensation on the scalp and to blind subjects as to the respective stimulation condition. Participants will be told about a mild tingling and itching sensation under the electrodes during the stimulation. After each active or sham tDCS session, participants will complete an adverse-effect questionnaire [33].

### Outcome measures and assessments

Outcome measures for the food cue-reactivity task (see Fig. 2) will be acquired pre- and post-fMRI at each session. At pre- and post-assessments, additional outcome measures targeting neural substrates will be assessed. The timeline of assessment measures is shown in Table 1. Each outcome measure will be analyzed regarding potential comparisons between the study groups (active vs. sham tDCS).

**Fig. 2 Fig2:**
[figure not shown]
Structure of the food cue-reactivity task. The task included food blocks and non-food blocks

**Table 1 Tab1:** Schedule of enrollment, interventions, and assessments

			Post-allocation							
			Baseline	Pre_**fMRI1**_	fMRI_**1**_	Post_**fMRI1**_	Intervention	Pre_**fMRI2**_	fMRI_**2**_	Post_**fMRI2**_
			~1 h	~10 min	~30 min	~10min	30 min	~10 min	~30 min	~25 min
Time point	Measurement	Mode	T0	T1	T2	T3	T4	T5	T6	T7
Enrollment										
Eligibility screening		Paper	X							
Informed consent		Paper	X							
Neuropsychological screening	Demographic data	Paper	X							
	EHI [34]	Paper	X							
	CES [35]	Paper	X							
	DASS-21 [36]	Paper	X							
	TFEQ-R-18 [37]	Paper	X							
	EDDS [38]	Paper	X							
	Food craving pictures	Tablet-PC	X							
Intervention							**↔**			
Viewing task	Food cue-reactivity	Computer			X				X	
Brain stimulation	tDCS (active vs. sham)	Device					X			
Questionnaires	FCQ-T [39]	Paper		X						X
	FCQ-S [40]	Paper		X						X
	Self-reported craving (VAS)	Paper		X		X		X		X
	Baseline hunger (VAS)	Paper		X		X		X		X
	Seven affective states (VAS)	Paper		X		X		X		X
	Blindness	Paper								X
	Sensations related to tES [33]	Paper								X
Additional assessments										
Physical measures	fMRI	Computer			X				X	
	DTI	Computer								X

*Abbreviations: EHI* Edinburgh Handedness Inventory, *CES* Compulsive Eating Scale, *DASS-21* Depression Anxiety Stress Scales-21, *TFEQ-R18* Three-Factor Eating Questionnaire-R18, *EDDS* Eating Disorder Diagnostic Scale, *FCQ-T* Food Craving Questionnaire-Trait, *FCQ-S* Food Craving Questionnaire-State, *VAS* Visual Analog Scale, *DTI* Diffusion tensor imaging

#### Primary outcomes

The primary outcome is the changes from pre-fMRI to post-fMRI in VAS scores (for food craving) at post-tDCS compared to changes at pre-tDCS in the sham and active tDCS groups.

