#### Pre- and post-assessments

The 0–100 continuous VAS will provide the possibility for assessing the self-reported food craving, hunger, and affective states in multiple time points before and after fMRI and tDCS (T1, T3, T5, and T7). Furthermore, FCQ-S and FCQ-T will provide the possibility for assessing the intensity of trait and state dimensions of food cravings before the first fMRI (T1: pre-tDCS) and after the second fMRI (T7: post-tDCS). Finally, participants will complete a questionnaire to assess blindness and potential adverse events of tDCS (T7).

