### Sample size estimation

Based on a recent study in the field using single-session bilateral tDCS over the DLPFC compared to sham tDCS [31], we estimated an effect size of 0.55. To demonstrate the intervention effect in the primary outcome, 64 participants (32 per tDCS group) need to be included in the analysis with a two-group *t*-test with a 0.05 two-sided significance level and a power of 80%. Sample size estimation was conducted using PASS software [47].

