### Statistical methods

Baseline participant characteristics will be presented as mean ± standard deviation for continuous variables or percentages for categorical variables. Participant demographics data will be compared between the active tDCS and sham tDCS groups, using a two-sample *t*-test (Student’s *t*-test).

To control for the tDCS intervention efficacy, a repeated-measures analysis of variance (ANOVA) will be performed on FCQ-T with time (before/after tDCS) as the within-subject factor and group (active tDCS/sham tDCS) as the between-group factor. The same strategy will be followed for behavioral and neuropsychological data.

Changes in functional neural parameters (resting-state and task-related fMRI) will be preprocessed and analyzed using the Analysis of Functional NeuroImages (AFNI) [48]. To assess brain–behavior associations, the correlations between changes in brain activity/connectivity and subjective craving will be investigated using the Pearson correlation test. As an exploratory analysis, the definition of major prognostic factors for response to active tDCS will be assessed using the exploratory regularized regression model. Assessment of the model validity will be performed using leave-one-out cross-validation within this dataset and will be validated with subsequent test datasets in the future studies. All statistical analyses will be run using the R Statistical Package [49]. There will be no interim analysis. The investigators will be empowered to stop the trial under the following circumstances:
Harm
There is a significant increased risk for serious adverse events, including severe itching and redness at the electrode site, nausea, dizziness, or drowsiness.Safety
Significant safety concerns emerge and the Research Ethics Committee of Iran University of Medical Sciences choose to pause or stop the trial.

We do not plan to conduct additional analyses, both subgroup and adjusted analyses.

We expect very low missing data in our baseline neuropsychological covariates and in the food craving measures (Table 1). Missing data will be reported in the publication. More than 5% missing data will result in multiple imputation with the generation of 40–50 imputed data sets to be analyzed separately and then aggregated into one estimate of the effect of the intervention on the primary and secondary outcomes. Missing data will be supplemented by the Multivariate Imputation by Chained Equations (MICE) method [50, 51].

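### The primary VAS outcome, read with the methods named, is an unadjusted double difference that adjustment for pre-tDCS craving would make more precise; separately, its starting point at T5 is already post-tDCS

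*Protocol article*

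**What the plan says.** All references are to the protocol article.

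- **Primary outcomes:** the outcome is "changes from pre-fMRI to post-fMRI in VAS scores (for food craving) at post-tDCS compared to changes at pre-tDCS", in the sham and active groups. No formula or model is attached.
- **Pre- and post-assessments, and Table 1:** the VAS is taken "in multiple time points before and after fMRI and tDCS (T1, T3, T5, and T7"). T1 and T3 lie either side of the first scan. Stimulation is at T4. T5 and T7 lie either side of the second scan.
- **Sample size estimation:** "we estimated an effect size of 0.55"; "64 participants (32 per tDCS group) need to be included in the analysis", by a two-group t-test "with a 0.05 two-sided significance level and a power of 80" per cent. The scale of 0.55 (raw score, change, or change of changes) is not stated.
- **Statistical methods:** a repeated-measures ANOVA "with time (before/after tDCS) as the within-subject factor and group (active tDCS/sham tDCS) as the between-group factor" is named for FCQ-T. It is then extended: "The same strategy will be followed for behavioral and neuropsychological data". The VAS is not mentioned by name. The section also says: "We do not plan to conduct additional analyses, both subgroup and adjusted analyses".
- **Background, list of aims:** one aim is to find out whether tDCS reduces food craving.
- **Secondary outcomes:** change in FCQ-S across stimulation, measured at T1 and T7.

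**The concern.** A t-test on a change, and the interaction in a two-level time-by-group ANOVA, are the same comparison. Applied to this outcome, both subtract T3−T1 from T7−T5 with a coefficient fixed at 1. Each change is a difference of single-item VAS readings and is likely to be noisy, so subtracting one from the other can add more noise than it removes. With 32 per arm, that could decide whether a real effect is detected.

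A second issue has a different cause. The post-stimulation change begins at T5, after the current has been delivered. Any effect already present at T5 is part of the starting value and drops out. The trial asks whether tDCS reduces craving, yet its primary VAS contrast registers only the part of the effect that develops between T5 and T7.

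**Working it through.** **The plan's own figure.** With d = 0.55, two-sided 0.05 and 80% power, the two-sample t-test needs 53 per arm (106 in total); the normal approximation gives 52 per arm. The stated 64 is not reproduced. At 32 per arm, power is 58%. That is a separate sample-size matter, used here only as the starting value.

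**Point 1: precision.** Let D1 = T3−T1 and D2 = T7−T5, with variances V1 and V2 within arm and correlation r.

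- Subtraction: Var(D2−D1) = V1 + V2 − 2r√(V1V2).
- ANCOVA of D2 on arm and D1: residual variance V2(1−r²).
- Subtraction minus ANCOVA: (√V1 − r√V2)², which is never negative.

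So, apart from one degree of freedom, ANCOVA is never less precise, whatever r is. D1 precedes stimulation, so under randomization both methods estimate the same arm difference.

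With V1 = V2 = V, the variances are 2V(1−r) and V(1−r²), and the ratio of ANCOVA to subtraction is (1+r)/2. The article gives no r, so the table shows an assumed range. Power is for a two-sided t-test with 32 per arm.

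- Scale A: 0.55 is in double-difference SDs. Subtraction uses d = 0.55; ANCOVA uses 0.55/√((1+r)/2).
- Scale B: 0.55 is in SDs of a single change. Subtraction uses 0.55/√(2(1−r)); ANCOVA uses 0.55/√(1−r²).

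| r | Variance ratio | A: subtraction | A: ANCOVA | B: subtraction | B: ANCOVA |
|---|---|---|---|---|---|
| 0 | 0.50 | 58% | 87% | 33% | 58% |
| 0.3 | 0.65 | 58% | 77% | 45% | 62% |
| 0.5 | 0.75 | 58% | 71% | 58% | 71% |
| 0.7 | 0.85 | 58% | 65% | 80% | 86% |

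The total N for 80% power on scale A is 106 by subtraction, against 54, 70, 80 and 92 by ANCOVA. On scale B it is 210, 148, 106 and 66 by subtraction, against 106, 98, 80 and 56.

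The case r = 0 is not contrived. If all four readings share one variance and one pairwise covariance c, then Cov(D1, D2) = c − c − c + c = 0. With first-order autoregressive correlation of 0.5 or 0.7 between adjacent readings, r is −0.125 or −0.105, and the ratio falls slightly below one half (0.44 or 0.45).

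**Point 2: the T5 starting point.** Suppose active tDCS lowers VAS by a at T5 and by b at T7, and sham does nothing. Randomization makes the expected arm difference in D1 zero, so the expected contrast is a − b under subtraction and under ANCOVA of D2 on D1.

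| Drop at T5 (a) | Drop at T7 (b) | Primary contrast (a − b) | Arm difference at T7 |
|---|---|---|---|
| 0 | 10 | −10 | −10 |
| 10 | 15 | −5 | −15 |
| 10 | 10 | 0 | −10 |
| 10 | 5 | +5 | −5 |

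A simulation with 200,000 participants agreed to within about 0.1 point for both methods. In the last row, a genuine reduction appears as an increase.

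**The case against.** **Subtraction is inferred.** The outcome definition says that one change is compared with the other and gives no formula, and the ANOVA is not tied to the VAS by name. A statistical analysis plan, not shown, may specify more. This stands as a limit. Still, neither method that the article names contains a covariate, so the double difference is its natural reading.

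**A reader might infer that the article forbids baseline adjustment.** It does not go that far. The sentence declines additional analyses, including adjusted ones, and need not cover a baseline term in the primary model. The problem is that no adjusted model is stated and the sentence can be read as excluding one.

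**A reader might infer that the variance is doubled as a matter of course.** Doubling is exact only at r = 0 with equal variances. At r = 0.7, subtraction inflates the variance by about 18% (1/0.85). The rise from 58% to 87% also requires 0.55 to be in double-difference SDs, which the article does not say.

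**A reader might infer that subtraction is what hides an early craving drop.** It is not. The cancellation comes from measuring the post-tDCS change from T5, and ANCOVA of T7−T5 has the same blind spot.

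**A general reduction would not vanish from the trial.** FCQ-S runs from T1 to T7 and could show it. Change across a cue-exposure scan is also a defensible measure of cue-induced craving, which the Discussion section names as a target. Both points stand. They limit the harm to the primary result; they do not remove the mismatch with the stated aim of reducing craving.

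**Conclusion.** Both points hold, and they are independent.

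1. On the natural reading, the primary VAS comparison is an unadjusted double difference. Adjusting for the pre-tDCS change would cut its variance by 50% at r = 0, 35% at 0.3, 25% at 0.5 and 15% at 0.7, assuming equal variances of the two changes. The direction of the gain is certain apart from one degree of freedom. Its size depends on r and, for power, on the scale of 0.55, neither of which the article gives.
2. The primary contrast is blind to any craving reduction that is equal at T5 and T7, and it reverses sign if an early reduction partly fades. Changing from subtraction to ANCOVA does not cure this. The loss is confined to the primary outcome, because FCQ-S spans the stimulation.

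This concerns the VAS outcome in the Primary outcomes section. The Abstract names a ventral striatum response as primary, a separate inconsistency on which this point does not depend. The changes are worth making, but nothing here shows the comparison to be invalid or biased.

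**What to change.** 1. State the model for the primary VAS outcome: ANCOVA of T7−T5 on arm, with T3−T1 as covariate instead of subtracted.
2. Reword the sentence on additional analyses in Statistical methods so that it clearly does not exclude this pre-specified baseline adjustment.
3. Report alongside it the arm differences in VAS at T5 and at T7, each adjusted for T1 and T3, with confidence intervals. Label them as supporting estimates, so that a general craving reduction is visible without adding another primary test.
4. State the scale on which 0.55 is measured, so that power can be judged for the model chosen.

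All four VAS readings are already scheduled in Table 1, so no new data are needed. The cost is wording and one or two residual degrees of freedom per model.

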#### Secondary outcomes

Change in FCQ-S scores from before tDCS to after tDCS, as measured by Food Craving Questionnaire-State [40]Change in resting-state functional connectivity between cortical and subcortical regions, as assessed by correlation between spontaneous BOLD signal fluctuations in subcortical ROIs and voxels within the prefrontal cortex and insula from before tDCS to after tDCSChange in resting-state functional connectivity under the stimulated area, as assessed by correlation between spontaneous BOLD signal fluctuations in the cortical area under the anode/cathode electrodes and whole brain from before tDCS to after tDCSChange in task-based functional activation in the prefrontal cortical areas and subcortical-limbic areas, as assessed by the BOLD signal changes with voxel-wise analysis in the regions of interests (ROIs) (prefrontal cortex, insula, thalamus, ventral striatum, and extended amygdala) from before tDCS to after tDCSChange in task-based functional connectivity between the cortical and subcortical regions, as assessed by psychophysiological interaction (PPI) between spontaneous BOLD signal fluctuations in subcortical ROIs and voxels within the prefrontal cortex and insula from before tDCS to after tDCSChange in task-based functional connectivity under the stimulated area, as assessed by psychophysiological interaction (PPI) between spontaneous BOLD signal fluctuations in the cortical area under the anode/cathode electrodes and whole brain from before tDCS to after tDCSChange in Resource Allocation Index (RAI) in rs-fMRI, as assessed by correlation among default mode network (DMN), saliency network (SN), and executive control network (ECN) in rs-fMRI from before tDCS to after tDCS [41]

#### Exploratory outcomes

Exploratory analyses will be conducted for measures of subjective, behavioral, neuropsychological, or neural circuits which will be analyzed for identifying potential predictors of food cue-reactivity task performance, and responsiveness to the intervention, as measures by an exploratory regularized regression model. Additionally, the induced E-field in the prefrontal area, derived from the analysis of the computational finite-element model, will be included as a potential predictor of neural response to tDCS [42, 43].

### Outcome assessments

The study timeline shown in Table 1 provides an overview of the time schedule of enrollment, interventions, and assessments.

#### Baseline assessments

At baseline assessment (T0), participants will be given written informed consent and complete a demographic questionnaire, a handedness inventory [34], Depression Anxiety Stress Scales-21 (DASS-21 [36]), Eating Disorder Diagnostic Scale (EDDS [38]), Compulsive Eating Scale (CES [35]), and Three-Factor Eating Questionnaire-R18 (TFEQ-R18 [37]). Afterward, participants will perform the food cue-reactivity training task to learn about the actual fMRI task (see the “Magnetic resonance imaging” section), which consists of one practice trial with 6 images of food and non-food products. The baseline assessment will take approximately 1 h.

#### Pre- and post-assessments

The 0–100 continuous VAS will provide the possibility for assessing the self-reported food craving, hunger, and affective states in multiple time points before and after fMRI and tDCS (T1, T3, T5, and T7). Furthermore, FCQ-S and FCQ-T will provide the possibility for assessing the intensity of trait and state dimensions of food cravings before the first fMRI (T1: pre-tDCS) and after the second fMRI (T7: post-tDCS). Finally, participants will complete a questionnaire to assess blindness and potential adverse events of tDCS (T7).

### Magnetic resonance imaging

MRI will be assessed at the Iranian National Brain Mapping Laboratory with a 3 Tesla scanner (Siemens Prisma) using a 20-channel head coil, prior to and immediately after intervention (see Table 2 for MRI data acquisition parameters).

**Table 2 Tab2:** MRI data acquisition parameters

Sequence	Main parameters
Resting-state fMRI	*TR = 2500 ms, TE = 30 ms, FOV = 192 × 192 mm*^*2*^*, 43 slices, 144 volumes, 3.0 × 3.0 × 3.0 mm*^*3*^*, flip angle = 90°*
Task-based fMRI	*TR = 2500 ms, TE = 23 ms, FOV = 192 × 192 mm*^*2*^*, 43 slices, 167 volumes, 3.0 × 3.0 × 3.0 mm*^*3*^*, flip angle = 70°*
DTI	*TR = 8000 ms, TE = 68 ms, 70 slices, 2 × 2 × 2 mm*^*3*^*, 64 directions (b = 1000 s/mm*^*2*^*)*
T1w	*TR = 1810 ms, TE = 3.45 ms, TI = 1100 ms, 176 slices, 1.03 × 1.03 × 1.0 mm*^*3*^*, flip angle = 7°*
T2w	*TR = 3200 ms, TE = 408 ms, 176 slices, 0.45 × 0.45 × 0.9 mm*^*3*^*, flip angle = 120°*

*Abbreviations: TR* Repetition time, *TE* Echo time, *TI* Inversion time, *FOV* Field of view, *fMRI* Functional magnetic resonance imaging, *DTI* Diffusion tensor imaging

Both MRI sessions include structural T1-weighted acquisition as well as resting-state fMRI to assess functional connectivity within and between large-scale networks that mediate food craving. Furthermore, a food cue-reactivity fMRI task will be used to assess intervention-associated changes in prefrontal functioning (see Fig. 2). At the end of the post-tDCS MRI assessment, additional T1- and T2-weighted images will be acquired with parameters optimized for computational finite-element method (FEM) modeling to calculate electric field strength and distribution induced by tDCS [44, 45]; see Fig. 3 for sample modeling analysis. After the MRI sessions, a separate DTI scan will be also performed to assess the structural integrity of the cortical-subcortical tracts, via quantification of fractional anisotropy [46]. In the food cue-reactivity task, participants will view 12 blocks of 6 images each (6 blocks with foods and 6 blocks with non-foods). Each block consists of 6 images of either food or neutral valence presented for 4000 ms with an interstimulus interval of 200 ms followed by an inter-block interval (i.e., gray screen with crosshair) with a duration (8–12 s). They will be given the following task instruction: “In the next task you will see food and non-food products. Please look at the images and pay close attention, since during the MRI session your job will be to press a button on the scroll wheel whenever you see the yellow border images.”

